## Abstract

Older adults have higher rates of emergency department (ED) admissions when compared to their younger counterparts. Mobility is the ability to move around, but also encompasses the environment and the ability to adapt to it. Walking aids can be used to improve mobility and prevent falls. According to international guidelines, they must be available in Geriatric EDs. This study aims to evaluate the efficacy of a program of training and provision of walking aids (WA), associated or not with telemonitoring, on fear of falling, mobility, quality of life and risk of falls up to 3 and 6 months in older adults cared for in an ED. A randomized controlled trial will be carried out in the ED. Participants will be randomized and allocated into three groups, as follows: A) walking aid group will be trained for the use of a walking aid and receive guidance on safe gait; B) walking aid and telemonitoring group will receive training for the use of a walking aid, guidance on safe gait, and telemonitoring (every two weeks for first three months); C) Control group will receive only guidance on safe gait. Patients will undergo a baseline evaluation encompassing sociodemographic and clinical data, mobility in life spaces, gait speed, muscle strength, functionality, quality of life, fear of falling, history of falls, cognition and mood before the intervention. Gait time and fear of falling will be assessed again after the intervention in ED. Finally, mobility in life spaces, functionality, quality of life, fear of falling, history of falls, cognition, and mood will be assessed 3 and 6 months after discharge from the geriatric ED through a telephone interview. Provision of walking aids in the geriatric ED is currently recommended. This study will be the first randomized controlled trial that will evaluate the impact of training and provision of these devices in the ED.

**Trial registration number**: NCT05950269.

## Introduction

According to the National Center for Health Statistics, a department of the Centers for Disease Control and Prevention (CDC) in the United States, people aged 74 and over represented 56.7% of all emergency department (ED) visits in 2018 [1]. Indeed, the ED plays an important role for the older patient, constituting not only an emergency treatment center, but also a point of entry for highly complex acute care, continued health care services, and 24-hour care [2, 3]. According to American Geriatric ED Guidelines, proper care for older patients require policies, protocols, and flows designed for the specific needs of this population [3]. More recently, European geriatric ED guidelines have promoted the “5 Ms of Geriatrics”: mind, medication, multi-complexity, “most important” and mobility [4].

Older adult’s health is associated with psychological, social, and environmental factors and chronic diseases, which impact mobility, functionality, autonomy, quality of life, and activities of daily living (ADL) [5]. Mobility is a term used not only to describe a person’s physical ability to move, but also encompasses the person’s environment and ability to adapt to it [6]. It can be assessed by the individual’s ability to move from furniture (bed or chair), walk and climb stairs. Correlated with mobility, the life-space is an emerging concept related to functional, environmental, and social factors that define how people experience their daily lives [7]. Acutely ill older people who are admitted through the ED for complaints associated or not with falls have a higher risk of falls, with an impact on functionality, quality of life, cognition, return visits, and mortality [8]. Because of this, it is essential that screening and assessments of mobility, gait quality, and risk of falls for this older population be incorporated into ERs and to implement safety, mobility, and quality of life measures for this older population, linked to adequate and safe use of auxiliary devices for the gait.

Finally, new technologies have been developed to improve health care, including telemonitoring. Telemonitoring is defined as the use of information technology and telecommunications for remote health care [9] and its main advantages are reducing unnecessary visits and home visits, reducing the risk of infections, monitoring the rehabilitation process, and improving patient compliance [10]. However, most studies related to telemonitoring are carried out with patients who have chronic diseases. Also, there are no data on the effects of an intervention encompassing gait devices, associated or not with telemonitoring, to improve the mobility of older patients admitted to the ED despite recommendations from international societies and the Geriatric Emergency Department Accreditation (GEDA) accreditation [3].

The hypothesis of the study is that the provision of walking aids enhances mobility in living spaces and will have a significant impact on fear of falling, functionality, and quality of life. Therefore, this study aims to evaluate the efficacy of a program of training and provision of walking aids, associated or not with telemonitoring, on fear falling, mobility, quality of life, and risk of falls up to 3 and 6 months in older adults cared for in an ED. In addition, we hypothesize that fear of falling may be correlated with lower scores in mobility, quality of life, and risk of falls.

## Materials and methods

### Study design

The present study is a randomized single-blind controlled trial, and it was approved by the Ethics Committee of the Hospital Sírio-Libanês (number 6.430.440), and the protocol design was registered in the Clinical Trials database (NCT05950269). This protocol was structured according to Standard Protocol Items: Recommendations for Interventional Trials (SPIRIT) (S1 File). As this is a study protocol, no data have been included and conforms to PLOS data policy. The overall schedule and time commitment for trial participants are depicted in Fig 1. The patients will be recruited by convenience from the geriatric ED of a philanthropic and tertiary hospital in São Paulo, Brazil, according to inclusion and exclusion criteria. The research structure is shown in Fig 2.

**Fig 1 pone.0304397.g001:**
[figure not shown]
SPIRIT diagram.

**Fig 2 pone.0304397.g002:**
[figure not shown]
Flow diagram of the clinical trial.

### Sample

Sample size calculation was based on Morgan and cols study, which described a minimal detectable change (MDC_95_) of 8,2 points on Falls Efficacy Scale International (FES-I), with a standard deviation of 12 points [11]. For the calculation, ANOVA sample size was used, and three groups were considered. For an α of 0.05 and a power of 0.80, the total sample size was computed as 42 individuals. Due to the estimated loss of 20% during follow-up, the sample necessary for the success of the study was expanded to 153 individuals, 51 in each group (randomization 1:1:1).

We will include patients aged 65 years or older, admitted to the Geriatric ED of Hospital Sírio-Libanês, willing and able to give informed consent and with at least one of the following for indication and training of mobility aids: reduction of postural instability; improvement of motor control; increase of somatosensory feedback; reduction of biomechanical overload; safe promotion of autonomy; fall history (in the last six months). Exclusion criteria will include altered level of conscience, need for supplemental oxygen (≥3L/min), respiratory distress, hemodynamic instability, postural instability with a tendency to fall backward, cognitive impairment that limits the use of walking aids, hospitalization after ED evaluation, and delirium.

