Telemonitoring has been more frequently studied in older adults, but mainly in ambulatory settings and focused on chronic illnesses [48–50]. In this study, the intervention will be evaluated in acutely ill older patients admitted to a Geriatric ED and trained in the use of walking aids. In addition, in a randomized clinical trial, telemonitoring could be an additional strategy to reduce the loss of follow-up of participants during the study.

Finally, to the best of our knowledge, there are no previous studies that have compared groups according to the provision of gait assistance devices and used FES-I as a main outcomes. Therefore, we’ve calculated the sample size using as a reference the study by Morgan et al. [11] which proposed a gait assistance device intervention in its participants and had a higher reported DMC than other initiative [51] but conducted intragroup comparisons. In addition, our study will also address intragroup differences when comparing baseline, 3 and 6 months after discharge from the geriatric ED.

A limitation of the study protocol is that it will be performed in a single center. However, having been described in detail, registered in a public database, and published in an open-source journal, it might be replicated by other research groups around the globe. In addition, another limitation of the study is that participants in the control group may initiate the use of assistive gait devices over the 6-month study period. However, this identification will be possible through the LSA questionnaire. After completion of the study and blind analysis of the data by the statistician, the percentage of individuals in the control group who initiated the use of gait devices will be shown. If there are patients in the control group who initiated the use of a gait device, it will be considered a protocol deviation from the assessment point at which they started using the assistive gait device, which may be 3 or 6 months after discharge from the geriatric ED service. Consequently, a secondary analysis will be presented without the protocol deviation values.

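### The computed sample size of 42 is labelled a total but is a per-group figure, and the 20% loss allowance was applied as × 1.2 instead of ÷ 0.8; the planned 153 is little affected

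*Protocol article*

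**What the plan says.** The justification is in the Sample section of Materials and methods. The effect size is a "minimal detectable change (MDC_95_) of 8,2 points on Falls Efficacy Scale International (FES-I"), "with a standard deviation of 12 points", both taken from one cited study. The method is given as follows: "ANOVA sample size was used, and three groups were considered". The result reads: "For an α of 0.05 and a power of 0.80, the total sample size was computed as 42 individuals". The next sentence reads: "Due to the estimated loss of 20% during follow-up, the sample necessary for the success of the study was expanded to 153 individuals", with 51 in each arm under 1:1:1 allocation.

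Fear of falling is the primary outcome (Outcomes section). The Statistical analysis section plans a one-way ANOVA, or Kruskal-Wallis for non-parametric data, for comparisons between groups. The Discussion says that no earlier study compared groups by provision of gait devices with FES-I as a main outcome. It adds that the reference study was chosen because it gave a gait device to its participants and "had a higher reported DMC than other initiative [51] but conducted intragroup comparisons".

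**The concern.** The two consecutive sample size sentences do not fit together. A 20% allowance on 42 gives 51 by multiplication or 53 by division; neither gives 153. One of the printed figures must therefore carry the wrong label.

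This matters because it is the only justification of size for the primary outcome. Read literally, the text says that 42 evaluable participants in all three arms together give 80% power, which the stated inputs do not support. The Discussion also suggests that other groups might replicate the protocol, and they could carry the figure over. Separately, an allowance made by multiplying by 1.2 does not leave the required number after 20% are lost.

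**Working it through.** **Inputs from the Sample section.** Difference d = 8.2; SD σ = 12; k = 3 groups; α = 0.05; power 0.80; loss 20%; 153 randomised, 51 per group.

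**Input not stated (assumption).** The pattern of the three means. I take 8.2 as the largest difference between any two arms and show two patterns:
- midpoint: means (0, 4.1, 8.2);
- two arms equal: means (0, 0, 8.2).

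**Formula.** Omnibus F test with n per group and noncentrality λ = n × Σ(μᵢ − μ̄)²/σ². Power = P[F′(2, 3n − 3; λ) > F critical at 0.05].
- Midpoint: Σ(μᵢ − μ̄)² = 8.2²/2 = 33.62; divided by 144 this is 0.2335, so f = √(0.2335/3) = 0.279.
- Two equal: Σ(μᵢ − μ̄)² = (2/3) × 8.2² = 44.83; divided by 144 this is 0.3113, so f = 0.322.

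**Step 1: reproduce 42.**

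| n per group | Total | Power, midpoint | Power, two equal |
|---|---|---|---|
| 14 | 42 | 32.4% | 41.9% |
| 40.8 | about 122 | 78.4% | 89.3% |
| 42 | 126 | 79.7% | 90.3% |
| 43 | 129 | 80.7% | 91.0% |
| 51 | 153 | 87.4% | 95.2% |

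The figure 42 is reproduced to within rounding as a number per group under the midpoint pattern; a strict 80% needs 43. With two equal means, 32 per group (96 in total) would be enough.

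No variant tried returns 42 in total. Means spaced 8.2 apart (0, 8.2, 16.4) need 36 in total. Setting f = 8.2/12 needs 24 in total. Two-group formulas, one-sided, two-sided or with α split for multiple comparisons, give 27 to 45 per group.

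**Step 2: reproduce 153.**
- 153/42 = 3.64, which a 20% allowance cannot produce.
- 42 × 1.2 = 50.4, rounded up to 51; 51 × 3 = 153. The chain closes only if 42 is per group.

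**Step 3: the loss allowance.**
- To retain 42 after 20% loss: 42/(1 − 0.20) = 52.5, so 53 per group; 53 × 3 = 159.
- Retained under the plan: 51 × 0.8 = 40.8 per group; 153 × 0.8 = 122.4 in total.
- Loss that 51 per group tolerates before falling below 42: 1 − 42/51 = 17.6%.
- Shortfall: 159 − 153 = 6 participants.

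**Step 4: effect on power.** At 20% loss, power is 78.4% for midpoint means. This is 1.6 points below 80% and 79.7 − 78.4 = 1.3 points below what 42 per group gives. With two equal means it is 89.3%.

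**The case against.** The strongest reply is that the trial will randomise 153, stated in the very next sentence as the number the study needs, so the mislabelled 42 never reaches recruitment. That stands. The 32% to 42% power would apply only if 42 participants in total were evaluated, and nothing in the article plans that.

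A reader might go further and infer that the trial will miss 80% power. The article does not support this. The pattern of means is unstated, and the result depends on it: about 78% for midpoint means, about 89% if two arms share a mean. With loss of 17.6% or less, the 42 per group is preserved. The benchmark of 42 itself gives 79.7%, so it would be inconsistent to accept that and call 78.4% a failure.

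A reader might also infer that using a within-person minimal detectable change as a between-arm difference is a concealed error. It is largely disclosed: the Sample section names the figure as an MDC95, and the Discussion explains why the study was borrowed and that its comparisons were within group. What remains is a preference about choice of effect size. A plain sentence calling 8.2 an assumed between-group difference would help, but its absence is not the fault raised here.

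What the reply does not answer is that the printed total is wrong and that the allowance does not deliver the retention it claims.

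**Conclusion.** Two stated figures are wrong. The 42 is a number per group (126 in total), not a total. The 51 per group comes from multiplying by 1.2, where retention of 42 after 20% loss needs 53 per group (159 in total). The first conclusion follows from the article's own arithmetic and does not depend on the pattern of means. The power values do depend on it, and on taking 8.2 as the largest difference between arms with a common SD of 12.

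The consequence is modest: a shortfall of 6 participants, and omnibus power at 20% loss of about 78% (midpoint means) to about 89% (two arms equal). This calls for a correction of the stated figures, with no change to conduct.

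It might be tempting to add that adjusting for baseline FES-I restores 80% at the planned size. That is true only conditionally. With midpoint means and 40.8 per group, a baseline-to-follow-up correlation of 0.1 gives 78.9% and 0.2 gives 80.2%. The article states no correlation, and its Statistical analysis section plans an unadjusted between-group test.

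**What to change.** Amend the Sample section as follows.

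1. Replace the total of 42 with 42 per group, 126 in total.
2. State the assumed pattern of means. With a largest difference of 8.2 and the third mean midway, 42 per group gives 79.7% power; 43 per group would be needed for a strict 80%.
3. Restate the allowance in one of two ways: 153 randomised tolerates 17.6% loss; or, at 20% loss, about 122 remain and omnibus power is about 78% for midpoint means.
4. Optionally, add that 8.2 is an assumed between-group difference taken from a within-person MDC95.
5. Make any statement about recovering power through baseline adjustment conditional on a correlation of about 0.2 or more and on adopting a baseline-adjusted analysis.

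The cost is a few sentences, and the stated power or tolerated loss becomes slightly less favourable. Enrolment can stay at 153. Only if the sponsor prefers to keep both the 20% allowance and 42 retained per group would the target become 159, six more participants.

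### The Sample section calls 42 the total sample size, but its inputs and its own expansion to 153 work only if 42 is the number per group

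*Protocol article*

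**What the plan says.** All of the sizing is in one paragraph of the protocol article, Materials and methods, Sample. It takes from a cited study a "minimal detectable change (MDC_95_) of 8,2 points on Falls Efficacy Scale International (FES-I" and pairs it "with a standard deviation of 12 points". The method is given as "ANOVA sample size was used, and three groups were considered". The result is stated as follows: "For an α of 0.05 and a power of 0.80", "the total sample size was computed as 42 individuals". The next sentence makes the allowance for attrition: "Due to the estimated loss of 20% during follow-up", the number was "expanded to 153 individuals, 51 in each group (randomization 1:1:1". The pattern of the three group means is not given.

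The calculation serves the primary outcome, fear of falling (Outcomes), which is measured by the FES-I (Fear of falling).

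**The concern.** The two sentences cannot both be right as worded. One gives a total of 42 before loss. The next gives 153 after an allowance of 20%, which is 153/42 = 3.64 times as many.

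This is the only justification of size in the document, and a reader cannot tell from it whether the evaluable number required is 42 or 126. The Discussion also says that the detailed description may allow other groups to replicate the study. Anyone who took the figure of 42 at face value would plan a trial one third of the size that these inputs call for.

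A smaller question follows: once 42 is read correctly, does the step from 42 to 51 per group actually absorb a 20% loss?

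**Working it through.** **Inputs** (all from Sample): largest difference d = 8.2; SD = 12; k = 3 groups; alpha = 0.05; power = 0.80; loss 20%; enrolment 153, or 51 per group. *Assumption:* d is the largest difference between any two groups. The position of the third mean is not stated, so both extremes are shown.

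**Step 1. Does the expansion fit a total of 42?**
- 42 × 1.2 = 50.4; 42 / 0.8 = 52.5. Neither is near 153.
- Per group: 42 × 1.2 = 50.4, rounded up to 51, and 51 × 3 = 153. This reproduces the stated figures exactly.

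**Step 2. Do the inputs give 42 in total or 42 per group?** For the one-way ANOVA with n per group, the noncentrality is λ = n × Σ(mean − grand mean)² / SD², and power is taken from the noncentral F with 2 and 3(n − 1) degrees of freedom.
- Third mean midway (0, 4.1, 8.2): λ = n × (4.1² + 0 + 4.1²)/144 = 0.2335n. This is the least favourable pattern for d = 8.2.
- One group differs (0, 0, 8.2): the grand mean is 2.733 and λ = n × (2 × 2.733² + 5.467²)/144 = 0.3113n. This is the most favourable.

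| n per group | Total | Power, midway | Power, one differs |
|---|---|---|---|
| 14 | 42 | 32.4% | 41.9% |
| 32 | 96 | – | 80% reached |
| 40.8 | 122.4 | 78.4% | 89.3% |
| 42 | 126 | 79.7% | 90.2% |
| 43 | 129 | 80.7% | 91.0% |
| 51 | 153 | 87.4% | 95.1% |

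The plan's 42 is therefore reproduced as a per-group number, to rounding, under the midway pattern; the exact F-test needs 43. A two-sample t-test at two-sided alpha 0.025 also gives 42 per group.

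No variant tried gives a total of 42. Entering f = 8.2/12 = 0.683 directly needs 24 in total. Means spaced 8.2 apart need 36. A total of 42 corresponds to f = 0.5, but with a largest difference of 8.2 and SD 12, f can be at most √(0.3113/3) = 0.32.

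**Step 3. Does 51 per group absorb 20% loss?**
- Completers at 20% loss: 51 × 0.8 = 40.8 per group; 153 × 0.8 = 122.4 in all, about 4 short of 126.
- To keep 42 per group: 42 / 0.8 = 52.5, so 53 per group, or 159 in all. The stated 153 is 6 fewer.
- Loss at which 153 still leaves 126: 1 − 126/153 = 17.6%.
- Cost in power under the midway pattern: 79.7% − 78.4% = 1.3 percentage points. If one group alone differs, power at 20% loss is about 89%.

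**The case against.** The strongest reply is that the size the plan commits to is 153, with 51 in each group, and that this figure is sound. It follows from 42 per group and gives about 80% power. Only an intermediate label is wrong. This stands, and it limits the weight of the point.

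A reader might go further and infer that the trial as planned has about a third of the power claimed, or that it could stop at 42 completers and still report 80% power. The document does not support either inference. Nothing in it makes 42 a stopping point, a completer threshold or a reporting criterion, and the same paragraph fixes 51 per group. The 32% to 42% describes a trial of 14 per group that nobody plans to run. It shows that the label is wrong and says nothing about the power of this study.

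A second reply concerns the loss allowance. The 20% is itself an estimate, the shortfall is about 4 patients in 126, and power falls below 80% only if the third mean is near the middle. That is also right. The midway pattern reproduces 42 and so was probably the one used, but the plan does not say so. What remains whatever the pattern is the arithmetic: multiplying by 1.2 does not leave 42 per group after a 20% loss.

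One might also defend 42 as a true total by supposing means spaced 8.2 apart, where 14 per group would give 88.6% power. That pattern puts the extreme groups 16.4 points apart, needs 36 and not 42, and leaves 153 unexplained.

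**Conclusion.** Wrong as written, of moderate severity. The figure of 42 is a per-group number labelled as a total; the evaluable total is 126. This rests on the expansion to 51 per group, which needs no assumption about the means, and on the power calculation, which takes 8.2 as the largest difference between groups.

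The loss allowance is a separate and minor slip. At the stated 20% loss, 153 leaves about 122 evaluable, and it preserves 126 only up to 17.6% loss. The effect is 1.3 points of power under the midway pattern.

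It would be too strong to conclude that 80% power does not follow from the inputs. Read as 42 per group it does follow before loss, to rounding (79.7%). After 20% loss power is about 78% to 89%, depending on the unstated pattern of means. Whether an MDC95 is a suitable between-group target is a different question and is not judged here.

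**What to change.** In Sample, replace the total of 42 with 42 per group, 126 evaluable in total. State the pattern of means assumed; if it is the third mean midway, note that 42 per group gives 79.7%. Keep enrolment at 153 and say what it delivers: 126 evaluable if loss is at most 17.6%, and about 122 at 20% loss, with power of about 78% (third mean midway) to 89% (one group differs by 8.2).

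The cost is a corrected paragraph and a slightly less favourable stated power. No extra patients are needed. The registry record and any analysis plan are not shown, so whether they carry the same wording is unknown; the sponsor can check.

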### Randomization and blinding

The process of randomization will be carried out by the software REDCap (automatically, without contact with the researcher) after the baseline evaluation. Subjects will be allocated to one of the intervention groups (1:1:1), which will have the same number of participants each: walking aid (WA) group; walking aid with telemonitoring (WAT) group; control group. The WA group will be trained for the use of a walking aid and receive guidance on safe gait but will not receive telemonitoring. The WAT group will receive training for the use of a walking aid, guidance on safe gait, and telemonitoring. The control group will receive only guidance on safe gait.

This study will be blind for the researchers involved in the post intervention assessments and the researcher who will analyze the data. Also, the data will be analyzed by a researcher who is not involved in the interventions nor the assessments.

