#### Mobility in life-space

Mobility in life space will be a secondary outcome of the study and will be assessed by the LSA, which allows the characterization of mobility in life-spaces (other rooms of your home besides the room where you sleep; to an area outside your home, places outside your neighborhood but within your town; and to places outside your town), specifically frequency, need for mobility aids and the help of third party in the last 4 weeks [14]. Four indicators are calculated (with the highest scores indicating greater life space):

Independent life-space: the highest life-space level attained without help from a person or mobility aid.Life-space using equipment: the highest life-space level attained when a mobility aid was used, without help from a person.Maximal life-space: the highest life-space level attained with the help of a person or mobility aid.Composite score: encompasses distance, frequency, and level of independence, with a range from 0 to 120.

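### Current cane or walker users can enter the control arm, but the plan's handling of control-arm aid use covers only controls who start a device after entry

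*Protocol article*

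**What the plan says.** All references are to the protocol article.

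- **Sample.** Patients aged 65 or older in the geriatric ED qualify "with at least one of the following for indication and training of mobility aids". A fall in the previous six months is one of the listed items and is enough alone. The exclusion list mentions walking aids once, in "cognitive impairment that limits the use of walking aids, hospitalization after ED evaluation, and delirium". Present use of a cane or walker is not listed.
- **Randomization and blinding.** Allocation is 1:1:1 through REDCap after the baseline evaluation, with no stratification factor named. "The control group will receive only guidance on safe gait".
- **Mobility in life-space.** The Life-Space Assessment (LSA) records "need for mobility aids and the help of third party in the last 4 weeks". Data handling and Assessment moments place it at baseline, before randomisation, and again at 3 and 6 months.
- **Discussion (limitations).** The risk named is that "participants in the control group may initiate the use of assistive gait devices over the 6-month study period". The percentage of controls who did so will be shown. For such a control, "it will be considered a protocol deviation from the assessment point at which they started using the assistive gait device", that point being 3 or 6 months, and "a secondary analysis will be presented without the protocol deviation values".

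**The concern.** The plan regards aid use among controls as serious enough to be a limitation, a protocol deviation and the reason for a secondary analysis. All of these depend on a control starting a device after entry. That presumes controls enter without one, which the eligibility criteria do not require.

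Take a woman who comes to the ED after a fall with her own cane and is allocated to control. At 3 months she is walking with a cane, as is a control who acquired one in the second month. Only the second is flagged, counted and removed from the secondary analysis. If there are many such women, the aid-versus-control difference in FES-I is diluted, the reported percentage understates device use among controls, and the analysis meant to show the effect free of such use still contains it. The contrast between the two aid arms (WA versus WAT) is not affected in this way, because both receive the device and the training.

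**Working it through.** **1. Does any rule reach a control who has an aid at entry?**

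| Rule | Trigger as written | Control who starts an aid later | Control with an aid at entry |
|---|---|---|---|
| Eligibility (Sample) | Listed exclusions | Not applicable | Not excluded |
| Allocation (Randomization and blinding) | 1:1:1, no factor named | Not applicable | Not balanced by design |
| Deviation (Discussion) | Starting a device | Flagged | Not flagged |
| Reported percentage (Discussion) | Starting a device | Counted | Not counted |
| Secondary analysis (Discussion) | Removes flagged values | Values removed | Values kept |

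No stated rule reaches her, although the baseline LSA would record her aid use.

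**2. The plan's own sample size.** Inputs from Sample: difference d = 8.2 FES-I points, SD 12, α = 0.05, power 0.80, three groups, one-way ANOVA.

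Power comes from the noncentral F distribution with 2 and 3(n − 1) degrees of freedom and noncentrality λ = n × Σ(mᵢ − m̄)² / SD².

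- Third mean midway (0, d/2, d): Σ = d²/2 = 33.62. With n = 42, λ = 42 × 33.62 / 144 = 9.81 and power is 79.7%.
- Both aid arms equal (0, d, d): Σ = 2d²/3 = 44.83. With n = 42, λ = 42 × 44.83 / 144 = 13.07 and power is 90.2%.

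Sample calls 42 the total. Read per group it gives the planned power under the midway pattern, and 42 × 1.2 = 50.4, rounded up to 51, × 3 = 153 is the stated final size. With 14 per group, power would be 32% (midway) or 42% (equal). I therefore use 42 per arm. The label is a separate matter. Taking 51 less 20%, about 41, changes little: 78.7% and 89.5%.

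**3. Dilution (assumption).** Let p be the share of participants already using an aid, equal across arms, and b the fraction of the full benefit that they gain when allocated to an aid arm. The average difference becomes 8.2 × [1 − p(1 − b)]. The document gives neither p nor b. I take p from 10% to 30% and b = 0 or 0.5.

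| p | b | Difference (points) | Power, midway | Power, aid arms equal |
|---|---|---|---|---|
| 0 | – | 8.20 | 80% | 90% |
| 10% | 0.5 | 7.79 | 75% | 87% |
| 10% | 0 | 7.38 | 70% | 83% |
| 20% | 0.5 | 7.38 | 70% | 83% |
| 20% | 0 | 6.56 | 59% | 73% |
| 30% | 0.5 | 6.97 | 65% | 78% |
| 30% | 0 | 5.74 | 48% | 60% |

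Example: p = 20%, b = 0 gives 8.2 × 0.8 = 6.56; midway λ = 42 × (6.56²/2) / 144 = 6.28, power 59%.

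**4. Precision if only baseline non-users are analysed.** At p = 20%, 42 × 0.8 = 33.6, so about 33 per arm. With the full 8.2 points, power is 69% (midway) or 81% (equal). Restricting the analysis removes the dilution but does not restore the planned power.

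**The case against.** A reader might infer that these controls already have the intervention. The document does not support that. The intervention is training plus provision, and under Training of walking aids a physical therapist identifies the need, chooses between cane and walker and teaches its use. A control with her own cane receives none of that, and a prior user allocated to an aid arm may receive a different device and is trained. So b = 0 is the pessimistic end, and the midway pattern is the least favourable to the F test for a given range of means.

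Nor is p known. The entry criteria make prior use plausible, but nothing in the document says how common it is.

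A reader might also infer that a null result could never be explained. That goes too far: the LSA is taken at baseline, 3 and 6 months, so aid use can be seen in every arm and examined afterwards.

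Adjustment and tabulation are often left to an analysis plan that is not shown, and the article may condense fuller eligibility criteria. That is fair for those items. It does not dispose of the point, because the article itself states the criteria and a specific rule for control aid use, and the two do not fit. If the full protocol excludes current users, the article should say so and the point closes.

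**Conclusion.** The gap is certain on the text; its size is not. Followed as written, the plan can enrol current aid users as controls, and its secondary analysis keeps them. They hold the device part of the intervention only.

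At an assumed 20% of prior users, 42 per arm and SD 12, power falls from 80% to 59–70% with the third mean midway, or from 90% to 73–83% with both aid arms equal. The lower end of each range assumes that prior users gain nothing and the upper end that they gain half the benefit. If few participants already use an aid, the effect is small.

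The document does not support concluding that the control arm is already treated, or that excluding current users is required.

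**What to change.** 1. **Derive** a yes/no variable for cane or walker use in the four weeks before entry from the baseline LSA.
2. **Stratify** the REDCap allocation by it. If recruitment has started, include it as a covariate in the between-group FES-I analysis instead.
3. **Extend the Discussion rule.** Report control aid use as prevalent at baseline plus newly started. Let the secondary analysis also cover controls already using an aid at baseline, by restricting all three arms to baseline non-users. Removing prior users from control alone would break the randomised comparison.
4. **State in Sample** whether current users are eligible.

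The data are already collected before randomisation, so the cost is one stratification factor, a little more analysis work, and lower precision in the non-user analysis (69% or 81% power at 20% prior users, as worked above). Excluding current users remains open to the sponsor. It would narrow the population, leave out people whose present aid is unsuitable or who were never trained in its use, and slow recruitment, so it is a choice and not a necessary correction.
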